## Abstract

**Background:**

Close contacts of individuals with active pulmonary tuberculosis (TB) face an elevated risk of TB acquisition, necessitating systematic screening for latent TB infection and subsequent TB preventive treatment (TPT). Major TPT regimens require ≥3 months of drug exposure and demonstrate suboptimal safety profiles, significantly compromising treatment completion rates. Therefore, the development of shorter, safer chemoprophylaxis strategies represents a critical need in global TB control. Among close contacts, school-aged children and adolescents constitute the most vulnerable demographic subgroup, warranting prioritized intervention efforts.

**Objective:**

The primary objective of this study is to demonstrate noninferiority of an ultrashort, 1-month TPT regimen of isoniazid plus rifapentine, administered 3 times a week (1H_3_P_3_) compared with the standard 3-month daily isoniazid plus rifampicin (3HR) regimen in preventing active TB, as measured by the 24-month cumulative incidence of active TB following randomization.

**Methods:**

An investigator-initiated, prospective, multicenter, open-label, noninferiority, cluster-randomized controlled clinical trial is being implemented under the auspices of the national TB control program in China. Close contacts of school pulmonary TB index cases, regardless of diagnostic type, are actively screened for symptoms using interferon-gamma release assays, chest imaging, and sputum molecular diagnostic testing to detect TB infection and exclude active TB. Eligible latent TB infection cases will be randomized in a 1:1 cluster ratio to receive either the standard 3HR regimen or the novel ultrashort 1H_3_P_3_ regimen for TPT, with subsequent follow-up for up to 2 years to assess disease progression. The primary composite end point includes microbiologically confirmed TB (sputum culture or molecular diagnostic testing) or clinically diagnosed TB. With 80% power to detect noninferiority (20% margin), the study requires 1760 participants per arm, accounting for cluster design effects.

**Results:**

Recruitment started in September 2023. By the end of December 2025, a total of 2478 participants, comprising 627 index cases, had been enrolled, and recruitment is estimated to continue until September 2026. Data analysis will commence after the 2-year follow-up period, and the results are expected to be published by March 2029.

**Conclusions:**

This cluster randomized controlled trial aims to establish the noninferiority of a novel, ultrashort 1H_3_P_3_ regimen compared to the standard 3-month 3HR regimen for preventing active TB in infected school contacts. If successful, this well-tolerated 1-month regimen could significantly improve treatment completion and optimize preventive therapy delivery in high-transmission congregate settings, thereby contributing substantively to global TB control efforts.

## Introduction

Latent tuberculosis infection (LTBI) refers to a state of persistent immune response to stimulation by *Mycobacterium tuberculosis* antigens without evidence of clinically manifest active tuberculosis (TB) and without bacteriological confirmation of active disease [1]. This immunological equilibrium can shift under conditions of waning host immunity, leading to active TB disease. On average, epidemiological data indicate a 5% to 10% lifetime risk of developing active TB, usually within 5 years after initial infection [1,2]. The incidence increases in high-risk populations, such as recent close contacts and immunocompromised individuals [3,4]. Screening and treating TB infection in the latent state are essential components of the World Health Organization End TB Strategy to prevent active disease [5]. Emerging transmission models suggest that a large proportion of transmission at the population level may occur outside the household [6]. This is particularly relevant in educational institutions, where congregate settings amplify transmission risk. For example, school-acquired infections constitute >50% of TB in adolescents (aged 15 to 19 years) [7].

TB preventive treatment (TPT) has been shown to effectively prevent adolescents with LTBI from progressing to active disease [8,9]. A TPT project conducted in Tibetan schools in India showed excellent efficacy, tolerability, and treatment adherence with the currently recommended 3-month daily isoniazid plus rifampicin (3HR) preventive therapy [10]. However, the same 3HR regimen for TPT has only resulted in low adherence and completion rates in practice in China, primarily attributed to its prolonged duration and drug-related toxicity [11]. To address these limitations, we propose a novel ultrashort 1-month TPT regimen of isoniazid and rifapentine, administered 3 times a week (1H_3_P_3_), through phased clinical development. In a pilot study, the regimen demonstrated improved safety and potentially superior efficacy compared to the 3-month isoniazid plus rifapentine regimen in patients with silicosis in Zhejiang province [12]. In particular, the treatment completion rate increased to >90%.

Therefore, we designed this trial to demonstrate the noninferiority of the ultrashort course of the 1H_3_P_3_ TPT regimen compared to the standard 3HR regimen in preventing active TB, as measured by the 24-month cumulative incidence of active TB following randomization. The findings will empirically define the clinical utility of accelerated TPT to support evidence-based clinical practice and policy development for TB elimination.

## Methods

### Study Design

This is a multicenter, prospective, cluster randomized, noninferiority clinical trial comparing the protective efficacy and safety of the 1H_3_P_3_ regimen with those of the 3HR regimen for TPT in adolescents and adults with LTBI. Prior to trial initiation, close contacts of pulmonary TB index cases within school environments will undergo active screening through the TB-YOUTH Screening program, a cross-sectional study (ClinicalTrials.gov NCT06033807), under the auspices of the National Tuberculosis Control Program in China. After excluding active TB, eligible LTBI participants will be grouped into clusters by their corresponding index cases. The clusters will then be randomized in a 1:1 ratio to receive either the 1H_3_P_3_ or the 3HR regimen for TPT. Medication adherence and adverse events (AEs) will be monitored at week 2, month 1, and month 2 for the 1H_3_P_3_ group, and at week 2 and then monthly until month 4 for the 3HR group after treatment initiation. Participants will undergo follow-up clinical assessments every 6 months for 2 years following randomization. The preventive efficacy of each study arm against active TB will be evaluated at the conclusion of the follow-up period.

### Description of Process

#### Identification of Index Cases and Contacts

The school contact screening cascade will be activated upon notification of active TB cases involving currently attending students or faculty members through the National Infectious Disease Surveillance System. Following verification by the local Centers for Disease Control and Prevention, comprehensive epidemiological and clinical data on the index case (eg, drug susceptibility profiles) will be systematically collected. Concurrently, TB screening will commence for school contacts of the index case. School contacts are defined in alignment with school TB prevention and control guidelines in China, which include teachers and students in the same class as the index case and students cohabiting in the same dormitory with the index case for at least 4 hours per week [13]. Operational definitions for screening algorithms are detailed in the TB-YOUTH Screening protocol.

#### Enrollment of LTBI Contacts

Contacts testing positive on QuantiFERON-TB Gold Plus (QIAGEN N V) will subsequently receive chest computed tomography (CT) or chest X-ray, as well as pooled sputum nucleic acid amplification testing (eg, GeneXpert MTB-RIF [Danaher Corp]) to exclude active TB. LTBI is defined as a positive interferon-gamma release assay result without evidence of active TB. Those with confirmed LTBI and aged ≥13 years are eligible for this trial. Study protocols will be thoroughly explained to eligible participants by site investigators, with written informed consent obtained prior to enrollment. Parental or guardian consent is mandatory for minors (aged <18 years). Participants meeting the inclusion criteria but declining enrollment in the TPT trial will be invited to join a supplemental nonintervention cohort. After providing separate informed consent, they will be followed for 24 months to monitor for the development of active TB. Further eligibility validations will require review of medical history and comprehensive laboratory evaluations to exclude contraindications to TPT. Textbox 1 shows the detailed inclusion and exclusion criteria.

Textbox 1.Inclusion and exclusion criteria for the TB-YOUTH study.
**Inclusion criteria**
Aged ≥13 years and body weight ≥30 kgSchool-registered individuals, including the following:Students currently attending junior high school, senior high school, or universitySchool staff membersClose contacts of active pulmonary tuberculosis (TB) index cases (microbiologically confirmed or clinically diagnosed) within the school, defined as meeting both the following criteria:Teachers or students sharing the same classroom or dormitory as the index caseExposure history defined as prolonged sharing of an enclosed space (>4 hours total within 1 week) with the index caseConfirmed latent TB infection (LTBI) status through screeningVoluntary participation with a signed informed consent form (for adults aged ≥18 years)Parental or guardian consent with cosigned informed consent form (for minors aged 13 to 17 years)
**Exclusion criteria**
Current active TB disease (clinically or bacteriologically confirmed)Documented isoniazid or rifampicin resistance in the corresponding *Mycobacterium tuberculosis* strain from the index caseSelf-reported use of rifamycins (eg, rifampicin or rifapentine) or isoniazid for >14 consecutive days within the past 2 yearsPrior completion of a full course of treatment for active TB or LTBIHypersensitivity or intolerance to rifamycins (rifapentine or rifampicin) or isoniazidHIV-positive serostatus or diagnosis of AIDSHistory of viral hepatitis (eg, chronic hepatitis B or chronic hepatitis C) or liver cirrhosisLiver dysfunction (total bilirubin >2.5 mg/dL [43 μmol/L] or alanine aminotransferase/aspartate aminotransferase >2×upper limit of normal) or renal dysfunctionCurrently receiving immunosuppressive therapy or biological agentsHematologic disorders, with either platelet count <50×10^9^/L or white blood count <3.0×10^9^/LOther conditions deemed unsuitable for TB preventive treatment by investigators

### TPT Intervention

Eligible participants, clustered by epidemiologically linked index cases, will undergo 1:1 randomization through an interactive web response system into 2 arms: the intervention arm will receive a 12-dose 1H_3_P_3_ regimen, and the active control arm will receive a 90-dose 3HR regimen. Intervention discontinuation should be considered under the following circumstances: (1) at any time upon request by the participant and/or their guardian, (2) major protocol deviation, or (3) an AE deemed by the safety review committee to result in an unfavorable risk-benefit profile for the participant. Interruption of one or more drugs of the assigned regimen consecutively for ≥1 month will be considered permanent discontinuation. Table 1 shows the detailed dosage and administration protocol of study drugs in each regimen. Any dose adjustment is strictly prohibited and will be considered a protocol deviation. All medications will be provided free of charge. TPT other than the assigned intervention is prohibited during the study.

**Table 1. T1:** Dosage and administration of study drugs for the 1H_3_P_3_ (1-month isoniazid plus rifapentine 3 times weekly) and 3HR (3-month daily isoniazid plus rifampicin) regimens.

Regimen and dosing categories (age and/or weight)	Dosage			Administration	Treatment course (months)
	Isoniazid	Rifapentine	Rifampicin		
1H_3_P_3_					
Weight 30-35 kg	300 mg	300 mg	N/A^a^	3 times weekly	1
Weight ≥35 kg	400 mg	450 mg	N/A	3 times weekly	1
3HR					
Age ≥18 years					
Weight <50 kg	300 mg	N/A	450 mg	Once daily	3
Weight ≥50 kg	300 mg	N/A	600 mg	Once daily	3
Age <18 years (weight-based dosing)	10 mg/kg^b^	N/A	10 mg/kg^c^	Once daily	3

a N/A: not applicable.

b Maximum dose of isoniazid=300 mg.

c Maximum dose of rifampicin=450 mg.

### Participant Monitoring and Support

All screened contacts will receive comprehensive TB education (eg, on-site education class, pamphlets, and digital resources) during initial and follow-up screenings. Participants enrolled in TPT will receive a standardized medication diary to log each administration (time, dose, and any AEs). Investigators will review entries prior to dispensing subsequent doses. A patient education booklet summarizing key TPT information (eg, frequently asked questions derived from the pilot study) will be distributed with the diary. Participants within clusters will be encouraged to select a peer coordinator to facilitate group medication adherence and foster a peer-supported compliance network.

### Follow-Up and Assessments

Participants in both study groups will undergo prospective monitoring comprising two phases: (1) on-treatment assessment (from enrollment to 1 month after treatment completion) and (2) posttreatment assessment (up to 24 months after randomization). On-treatment assessments will involve standardized clinical evaluations, including physical signs, laboratory testing, medication adherence (pill counts and self-reporting), and safety monitoring, and will be scheduled at week 2, month 1, and month 2 for the 1H_3_P_3_ arm, and at week 2, then monthly until month 4 for the 3HR group. On the basis of recommendations from the independent protocol review board, and to comprehensively evaluate the impact of interventions on quality of life, a protocol amendment was implemented after approximately 2300 participants had been enrolled. Following ethics committee approval, the EuroQol 5-Dimensions 3-level questionnaire (version 6.0, December 2018) was incorporated as an exploratory end point. This questionnaire will be administered at every on-treatment assessment for participants enrolled after the amendment’s effective date. Posttreatment assessment will focus on active TB surveillance as well as delayed AE monitoring and will occur every 6 months from randomization until study exit. At each visit, participants will receive a standardized symptom screening for active TB, including persistent cough (≥2 weeks), fever, night sweats, weight loss, hemoptysis, or other TB-associated symptoms. Participants with positive symptom screens will undergo confirmatory sputum culture and molecular diagnostic testing. The end point adjudication committee will determine the final active TB diagnosis per predefined criteria.

The schedule of this study is summarized in Table 2.

**Table 2. T2:** SPIRIT (Standard Protocol Items: Recommendations for Interventional Trials) diagram showing enrollment, intervention, and assessment procedures.

	Enrollment	Allocation	Postallocation phase						Closeout
Time point^a^	–30 days	0 day	2 weeks	1 month	2 months	3 months	4 months	Every 6 months	24 months
Enrollment									
Eligibility screening	✓								
Informed consent	✓								
Medical history	✓								
Allocation		✓							
Interventions									
1-month isoniazid plus rifapentine 3 times weekly regimen		↔^b^	↔	↔					
3-month daily isoniazid plus rifampicin regimen		↔	↔	↔	↔	↔			
Assessments^c^									
Demographic characteristics and medical history	✓	✓							
Treatment adherence			✓	✓	✓	✓			
Safety monitoring			↔	↔	↔	↔	↔		
Tuberculosis surveillance		↔	↔	↔	↔	↔	↔	↔	↔

a This row displays specific time points relative to randomization. Acceptable time window: more or less than 7 days for the intervention period and more or less than 30 days for the postintervention phase.

b ↔: this arrow represents continuous interventions.

c On-treatment assessments and 1-month posttreatment assessments require in-person attendance, whereas postintervention assessments may be conducted in person or remotely.

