### Study Objectives and End points

The primary objective is to demonstrate noninferiority of the ultrashort course of the 1H_3_P_3_ TPT regimen compared with the standard 3HR regimen in preventing active TB, as measured by the 24-month cumulative incidence of active TB following randomization. The secondary objectives include: (1) to compare safety, patient-reported quality of life, and treatment discontinuation rates attributable to AEs between the regimens; (2) to evaluate treatment adherence using protocol-defined completion criteria; (3) to assess acquired *M tuberculosis* drug resistance among participants who develop active TB after TPT; and (4) to establish a contemporary nonintervention cohort for exploratory comparison, delineating the natural progression to active TB among individuals with high-risk LTBI in whom active TB has been ruled out.

The primary end point is a composite of bacteriologically confirmed or clinically diagnosed active TB within 24 months after randomization. Bacteriologically confirmed active TB refers to *M tuberculosis* identification via ≥1 sputum culture and/or molecular assay (eg, GeneXpert MTB-RIF) with detectable bacterial load. Clinically diagnosed TB combines objective clinical symptoms (≥2 of the following: cough ≥2 weeks, fever, night sweats, weight loss >10%, or hemoptysis) and imaging findings highly suggestive of active TB (eg, cavity or nodular lesions on chest CT), after exclusion of alternative diagnoses. Secondary end points include severity-graded AEs, treatment discontinuation (defined as any permanent cessation prior to regimen completion), treatment completion (defined as completing ≥90% of scheduled doses within 110% of the planned treatment duration), all-cause mortality, and acquired drug resistance determined by drug susceptibility testing or targeted molecular assays of *M tuberculosis* isolates from active TB cases. Exploratory analysis will use the nonintervention cohort to establish the background incidence of active TB, against which the risk reduction of each TPT regimen can be calculated. Patient-reported outcomes (PROs) will be calculated using health state utility values and EuroQol visual analog scale scores.

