For secondary end points, all AEs, serious AEs (SAEs), and treatment discontinuations due to AEs will be documented. Group differences in AE proportions will be analyzed using the chi-square test or Fisher exact test (2-sided *α*=.05). Treatment completion is defined as consuming ≥90% of planned doses within 110% of the planned treatment duration (≥11 doses within 6 weeks for the 1H_3_P_3_ group and ≥81 doses within 16 weeks for the 3HR group). The 2-year cumulative incidence of active TB in the nonintervention cohort will be calculated using the Kaplan-Meier method, with 95% CI estimated. The protective efficacy of the 1H_3_P_3_ and 3HR regimens relative to the nonintervention cohort will be quantified as the risk reduction rate: 1–(intervention group incidence/nonintervention group incidence). The Fisher exact test will be used to compare incidence differences among the 3 cohorts.

All analyses concerning the PRO end point will be explicitly restricted to the subgroup of participants who complete the EuroQol 5-Dimensions 3-level questionnaire. The baseline characteristics of this PRO subgroup will be compared between the 2 arms to confirm that randomization balance was maintained. Any interpretation of PRO findings will explicitly acknowledge their exploratory nature and the fact that they are derived from a subset of the total study population. Trends in PRO metrics over time will be visualized using line graphs, with mean values and 95% CIs plotted to illustrate group-level changes. A mixed-effects model for repeated measures will be used to compare PRO differences between the 1H_3_P_3_ and 3HR groups across time points, with fixed effects including treatment group, assessment time point, treatment group×time point interaction, age, sex, BMI, and index case cavitation status, and a random participant-specific intercept to account for within-subject correlation from repeated assessments.

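### EQ-5D-3L visits follow arm-specific schedules with no day-0 form listed, so the planned treatment-by-time comparison can be estimated only at week 2, month 1 and month 2, without baseline adjustment

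*Protocol article*

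**What the plan says.** All references are to the Protocol article.

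- **When the form is given.** Follow-Up and Assessments: "This questionnaire will be administered at every on-treatment assessment for participants enrolled after" (the sentence then names the date on which the amendment took effect). The amendment came after about 2300 participants had been enrolled.
- **Which visits those are.** For 1H3P3, the same section states that on-treatment evaluations "will be scheduled at week 2, month 1, and month 2 for the 1H_3_P_3_ arm". For 3HR it gives a longer series of five visits: week 2 and months 1, 2, 3 and 4. Study Design lists the same visits. Later visits, every 6 months, are described as covering TB surveillance and delayed adverse events. The questionnaire is not mentioned for them, and Table 2 has no row for it.
- **How the scores are analysed.** Statistical Analysis plans a mixed model for repeated measures that compares the arms over the time points, "with fixed effects including treatment group, assessment time point, treatment group×time point interaction", plus age, sex, BMI and index case cavitation. No baseline EQ-5D score is among the terms. Line graphs are to show change by group.
- **What status the outcome has.** Study Objectives and End points places it in secondary objective (1): "to compare safety, patient-reported quality of life, and treatment discontinuation rates attributable to AEs between the regimens". The list of secondary end points in that section omits it. Follow-Up and Assessments and Statistical Analysis both call it exploratory.

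**The concern.** The data collection and the model do not fit each other. The model crosses arm with time point, but two of the time points exist in one arm only. An analysis plan can choose how to code time, but it cannot supply scores that were never collected.

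The quality-of-life case for a 1-month regimen rests largely on the period when its recipients have finished and the 3-month group is still taking tablets. Part of that period is measured in one arm only.

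The first listed score comes at week 2, when a 1H3P3 participant has taken about 6 of 12 doses. There is then no pre-treatment value from which to plot change, to adjust for, or to check that the subgroup was balanced on quality of life itself. Statistical Analysis does intend to check the balance of baseline characteristics in this subgroup.

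**Working it through.** The plan gives no power or sample size figure for the EQ-5D comparison, so there is nothing to reproduce. The check sets the visit schedule against the model.

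**1. Visits by arm.** Schedules are from Follow-Up and Assessments. Treatment lengths of 1 and 3 months are from Table 1.

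| Visit | 1H3P3 | 3HR | Form scheduled in | Between-arm contrast |
|---|---|---|---|---|
| Week 2 | on drug | on drug | both | yes |
| Month 1 | end of course | on drug | both | yes |
| Month 2 | off drug | on drug | both | yes |
| Month 3 | off drug | end of course | 3HR only | no |
| Month 4 | off drug | off drug | 3HR only | no |

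**2. Estimability.** A full arm-by-time model over five visits has 5 time means + 5 arm differences = 10 parameters. The observed cells number 3 (1H3P3) + 5 (3HR) = 8. The design matrix has 10 columns and rank 8. The two parameters that cannot be estimated are the arm differences at months 3 and 4. The other three arm differences are estimable.

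**3. Off-drug versus on-drug visits.** Counting month 3 as the end of 3HR dosing, there are two such visits, months 2 and 3. One of the two is measured in both arms.

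**4. Timing of the first score.** 3 doses per week × 2 weeks = 6 of 12 doses.

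**5. Size of the subgroup.** Planned enrolment is 2 × 1760 = 3520 (Randomization and Sample Size Calculation).
- Largest possible questionnaire subgroup: 3520 − 2300 = 1220, and 1220/3520 = 34.7%, or about 610 per arm.
- Still to be enrolled at the end of December 2025 (Results gives 2478 enrolled): 3520 − 2478 = 1042.
- Enrolled between the amendment and that date: 2478 − 2300 = about 178.

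On these figures about 1042 of 1220 (85%) could still have had a day-0 score at that date. The 2300 is approximate in the article. The calculation also assumes that 2478 counts trial participants only.

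**6. What a baseline score could add.** If the baseline-to-follow-up correlation is ρ, adjustment lowers residual variance by ρ². The article gives no value. For an assumed ρ of 0.4 to 0.6 the reduction is 0.4² = 16% to 0.6² = 36%. This only illustrates the possible gain in precision.

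**7. Effect of a common schedule.** If 1H3P3 also had the form at months 3 and 4, the rank would be 10 of 10 and all five contrasts would be estimable.

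**The case against.** **The stronger reading.** A reader might infer that the comparison cannot be made at all where the regimens differ most. The documents do not support that. Month 2 is scheduled in both arms, with 1H3P3 finished for about a month and 3HR still being taken. Month 3 would largely repeat that contrast at the end of 3HR dosing. At month 4 both arms are off drug.

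**No baseline is inferred from silence.** The phase is defined as "on-treatment assessment (from enrollment to 1 month after treatment completion", and a journal article need not print every form schedule. This stands in part. The accurate statement is that no day-0 administration is listed, not that one is excluded. However, the article does list the visits at which the form is given and the covariates in the model, and a baseline score is in neither list.

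**A baseline is not needed for validity.** This stands. Randomised arms can be compared at shared visits without one, so the loss is mainly in precision, in plotting change and in checking balance. A baseline is somewhat more useful than usual here. The trial is open-label, a cluster is randomised once at least one member is enrolled, and the analysis is restricted to those who complete the form. The article does not say whether later members of a cluster join knowing their arm, so no bias can be asserted.

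**The model does not fail.** This stands too. It still yields the three shared-visit contrasts, and no month 3 or month 4 contrast is named. The difficulty is that the analysis is described as running over the time points without limiting it to the shared ones.

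**The 35% ceiling has another cause.** It comes from the timing of the amendment, and the article already acknowledges that the findings come from a subset.

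**Conclusion.** The point holds as a mismatch between schedule and model. Between-arm contrasts are estimable at 3 of 5 visits, and at 1 of the 2 visits where one arm is off drug and the other on. On the schedule as listed, change from baseline and baseline adjustment are not available. The quality-of-life comparison can still be made, and is valid, at week 2, month 1 and month 2.

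This rests on the listed visits being the complete questionnaire schedule. If the full protocol includes a day-0 form, the baseline part falls away and only the month 3 and 4 part remains.

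The outcome is described as exploratory, is limited to at most about 35% of planned participants, and has no bearing on the primary noninferiority result. The point is minor to moderate. The inconsistent label, within a secondary objective in one section and exploratory in two others, is a separate wording fault.

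**What to change.** 1. **Add a day-0 form.** For participants still to be enrolled, give the EQ-5D-3L at day 0 before the first dose. Add the baseline score as a covariate in the mixed model. State how its absence is handled for questionnaire participants enrolled before the change, for example with a missing-baseline indicator and a sensitivity analysis in those who have a score.
2. **Name the contrasts.** Define the between-arm contrasts as week 2, month 1 and month 2 only, and report 3HR months 3 and 4 descriptively. Alternatively, collect the form in both arms at months 3 and 4 by the same mode. The mode matters: a footnote to Table 2 requires in-person attendance for on-treatment and 1-month posttreatment assessments but allows remote contact later. Remote forms for 1H3P3 set against in-person forms for 3HR would make mode differ by arm at exactly the added visits.
3. **Reconcile the labels.** Make the status of quality of life the same in Study Objectives and End points, Follow-Up and Assessments, and Statistical Analysis.

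**Cost.** A short amendment with ethics approval and one brief form at an existing contact. Questionnaire participants already enrolled (about 178 by the end of December 2025) will have no baseline score, and that number grows until the change takes effect. Item 2 in its first form and item 3 cost only wording. The alternative in item 2 adds two contacts for each remaining 1H3P3 participant.
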